The EQ-5D-5L is a self-reporting questionnaire applied to evaluate quality of life. It comprises five dimensions as follows: mobility, self-care, usual activities, pain/discomfort, and anxiety/depression [25]. In addition, participants’ self-rated health status will be recorded on a vertical VAS scale drawn from 0 (the worst health you can imagine) to 100 (the best health you can imagine). It will be assessed at all visits except the screening visit.

(7) Spleen Qi Deficiency Questionnaire (SQDQ)

The SQDQ consists of 11 items associated with symptoms such as loss of appetite, reduced food intake, and general fatigue, evaluated on a 5-point scale [26]. After applying weight conversion to each question, if the total score exceeds 43.18 points, the participants will be diagnosed as spleen qi deficiency [27]. Data will be collected at baseline (Visit 2), week 3 (Visit 3), and week 6 (Visit 4).

(8) Damum Questionnaire (DQ)

The DQ is an instrument for determining if a participant has symptoms of phlegm pattern such as dizziness, chest discomfort, and indigestion. It includes a total of 14 items on the basis of a 7-point scale. Higher scores calculated by multiplying the weights indicate a high possibility of the existence of Damum [28]. The DQ will be evaluated at baseline (Visit 2), week 3 (Visit 3), and week 6 (Visit 4).

(9) Serum Ghrelin Levels

We will evaluate serum levels of acyl-ghrelin and deacyl-ghrelin, and the ratio of acyl-ghrelin to total ghrelin by collecting serum acyl-ghrelin and deacyl-ghrelin at the screening visit and week 6 (Visit 4).

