**Hypothesis** **1.**
*[*

$H_{0}\;:\;\mu_{1}=\mu_{2},\;H_{1}\;:\;\mu_{1}\neq \mu_{2}$

*]*

*-*

$\mu_{1}$

*: Change in TDS score of the YGJ group at week 6*

*-*

$\mu_{2}$

*: Change in TDS score of the usual care group at week 6*

A two-sided test with a significance level of 5% will be conducted using a mixed-effect model repeated measure (MMRM) with participants as the random factor and the treatment group and time of visit as the fixed factors. If necessary, analyses will be performed by setting variables showing statistically significant differences in demographic characteristics or variables that can affect dyspepsia as the fixed factors. The second purpose of this study is to evaluate the noninferiority of YGJ compared to that of PWS (Hypothesis 3). Consequently, the noninferiority margin (*M*) will first be defined based on the results of the effect evaluation of PWS compared to usual care at week 6 (Hypothesis 2), and the analysis method will be the same as that of Hypothesis 1.

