Other secondary outcome measures will be tested in the same way as the primary outcome measure. In addition, to compare the difference between the values before and after treatment in each group, the continuous variable will be analyzed using Student’s paired *t*-test or Wilcoxon signed-rank test, and the discrete variable will be Fisher’s exact test. Repeated measures analysis of variance will be performed to compare the differences in trend change in each group of visits, and Dunnett’s procedure (based on the baseline) will be used as a multiple comparison correction.

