## Figures and Tables

**Figure 1 healthcare-11-01456-f001:**
[figure not shown]
Flow chart of the trial process.

**Table 1 healthcare-11-01456-t001:** Schedule of enrolment, interventions, and assessments.

	Study Period					
	Enrolment	Allocation	Medication		Follow-Up	
Procedures	Visit 1 (Screening)	Visit 2	Visit 3	Visit 4	Visit 5	Visit 6 (Telephone)
TIMEPOINT	−2 weeks	Week 0	Week 3 ±4 days	Week 6 ±4 days	Week 9 ±4 days	Week 24 ±4 days
ENROLLMENT						
Eligibility screen	●					
Informed consent	●					
Demographics	●					
Medical and treatment history	●					
Physical examination	●					
Vital signs	●	●	●	●	●	
PIFD	●					
Allocation		●				
INTERVENTIONS						
YGJ or PWS		○	○	○		
Dietary guideline education		●	●	●		
ASSESSMENTS						
TDS		●	●	●	●	●
SDS		●	●	●	●	
OTE			●	●	●	●
VAS (dyspepsia)	●		●	●	●	
FD-QoL		●	●	●		
HADS	●		●	●	●	
EQ-5D-5L EQ-VAS		●	●	●	●	●
SQDQ		●	●	●		
DQ		●	●	●		
Cost questionnaire		●	●	●	●	●
Laboratory tests *	●			●		
Adverse events investigation		●	●	●	●	
Compliance test			○	○		

●: all participants, ○: YGJ and PWS groups, * Including hematological, blood glucose level, liver and renal function tests, electrolyte test, acyl-ghrelin, and deacyl-ghrelin. In addition, human chorionic gonadotropin urine test for women in their childbearing years, and anti-*Helicobacter pylori* serum IgG testing at the screening visit. Abbreviations. DQ, Damum questionnaire; EQ-VAS, the EuroQol visual analog scale; EQ-5D-5L, five-level version of the EuroQol five-dimensional descriptive system; FD-QoL, functional dyspepsia-related quality of life; HADS, hospital anxiety and depression scale; OTE, overall treatment effect; PIFD, pattern identification of functional dyspepsia; PWS, Pyeongwi-san; SDS, single dyspepsia symptom; SQDQ, spleen qi deficiency questionnaire; TDS, total dyspepsia symptom; VAS, visual analog scale; YGJ, Yukgunja-tang.

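### Serum ghrelin, with one screening and one week-6 value, is assigned to the primary repeated-measures model, which does not suit it; ANCOVA on the screening value would

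*Protocol article*

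**What the plan says.** Serum ghrelin is the ninth secondary outcome in section 2.9.3 of the protocol article. The plan is to evaluate both forms and "the ratio of acyl-ghrelin to total ghrelin by collecting serum acyl-ghrelin and deacyl-ghrelin at the screening visit and week 6 (Visit 4"; there is no other sample. Table 1 agrees: the footnote to the laboratory row reads "Including hematological, blood glucose level, liver and renal function tests, electrolyte test, acyl-ghrelin, and deacyl-ghrelin", and that row is marked at Visits 1 and 4 only.

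Section 2.11 gives ghrelin no model of its own. It has a general rule: "Other secondary outcome measures will be tested in the same way as the primary outcome measure". The primary method, under Hypothesis 1, is a "mixed-effect model repeated measure (MMRM) with participants as the random factor and the treatment group and time of visit as the fixed factors", and the hypotheses concern change, for example "Change in TDS score of the YGJ group at week 6". The stated model has no group-by-visit term and no covariate for the outcome's own pre-treatment value. For before/after differences inside each group, section 2.11 adds that "the continuous variable will be analyzed using Student’s paired *t*-test or Wilcoxon signed-rank test".

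The Discussion (section 3) says that earlier ghrelin work was inconclusive because specimens were few. It plans to use the ghrelin changes to explore whether YGJ and PWS act by different mechanisms.

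**The concern.** The primary outcome is measured at weeks 0, 3, 6, 9 and 24, so a repeated-measures model has something to work on. Ghrelin has a single value after treatment. A rule written for a score with several post-treatment visits is applied unchanged to an outcome that has only one.

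At stake is how well a small sample answers the mechanism question. Section 2.10 plans for 44, 44 and 22 evaluable participants. The stated rule makes no use of the screening value as a covariate, although it is collected from everyone. On one reading, its group effect does not measure the treatment effect at week 6 at all.

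**Working it through.** **Inputs.** From the documents: ghrelin at screening and week 6 (section 2.9.3, Table 1); participant random, group and visit fixed (section 2.11); two-sided 5%; 44, 44 and 22 evaluable (section 2.10). Assumed, because the documents give no ghrelin figures: equal variance σ² at both times, screening-to-week-6 correlation ρ of 0.5 to 0.8, complete data, and no expected group difference at screening (which follows from randomisation).

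**The plan's own figure.** The only calculated sample size is for TDS. Usual care n = (1.960 + 0.842)² × 3.65² × (1 + 1/2) / 2.70² = 21.5, so 22, with 44 for YGJ. This matches the article. No calculation is given for ghrelin.

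**Reading A: change is the response.** Each participant gives one record and visit has one level.
- The visit effect drops out.
- Participant variance cannot be separated from residual variance. In a simulated data set (44 versus 22), the fit split the ordinary residual variance of 0.544 arbitrarily into 0.272 + 0.272 and warned of a Hessian that was not positive definite.
- The standard error of the group effect was 0.193, the same as in a plain two-sample comparison of change. The group test survives but is unadjusted.

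**Reading B: both values are responses.** The model converges. With only group and visit fixed, the group effect is the group difference averaged over screening and week 6. If δ is the week-6 effect, its expected value is (0 + δ)/2 = δ/2. In the same simulated set the screening difference was 0.124 and the group-by-visit term 0.299; the main-effects model returned 0.124 + 0.299/2 = 0.274. With a group-by-visit term added, the estimate is 0.299 with standard error 0.193, which is Reading A again.

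**Size.** Let k = √(1/n₁ + 1/n₂). The expected z-values are:
- ANCOVA of week 6 on screening: δ / [σ k √(1 − ρ²)]
- unadjusted change: δ / [σ k √(2(1 − ρ))]
- group term in Reading B: (δ/2) / [σ k √((1 + ρ)/2)]

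Relative to ANCOVA, the z-value is multiplied by √((1 + ρ)/2) for change and by √((1 − ρ)/2) for Reading B. Both factors are free of k, so they apply to YGJ versus PWS as well as to YGJ versus usual care. Set ANCOVA at 80% power, so that its z-value is 1.960 + 0.842 = 2.802:

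| ρ | Change: factor, z, power | Reading B: factor, z, power |
|---|---|---|
| 0.5 | 0.866, 2.426, 68% | 0.500, 1.401, 29% |
| 0.7 | 0.922, 2.583, 73% | 0.387, 1.085, 19% |
| 0.8 | 0.949, 2.658, 76% | 0.316, 0.886, 14% |

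A simulation of 4,000 runs per setting at 44 versus 22 agrees for change: 66% to 68% at ρ = 0.5 and 72% to 74% at ρ = 0.7 on the log scale, with log ANCOVA at 77% to 80%.

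**Scale.** For assumed log-normal levels, with the effect set for 80% nominal power under log ANCOVA, the loss from untransformed ANCOVA, over ρ of 0.5 and 0.7 and over 44 versus 22 and 44 versus 44, was:

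| CV | Loss in power (points) |
|---|---|
| up to 0.31 | 1 to 5 |
| about 0.5 | 6 to 10 |
| about 0.8 | 12 to 18 |
| about 1.3 | 24 to 33 |

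**The case against.** A reader might infer that the model cannot be fitted. That goes too far. On the two values it fits and converges; on change it collapses to a two-sample comparison whose group test is intact. The hypotheses are worded as change at week 6, so an analyst would probably arrive at that comparison, and the loss would then be the smaller one in the first table. The missing group-by-visit term also concerns the primary model and is not special to ghrelin.

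A reader might also infer that ghrelin will be analysed on the raw scale at a known cost in power. The article names neither a raw nor a log scale, and a transformation is commonly left to an analysis plan that is not shown. The losses by CV rest on a log-normal distribution and a proportional effect, which favour logging by construction, and they are small at low CV. None of them covers the acyl share, which lies between 0 and 1.

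The plan does offer a rank test for before/after change, which fits part of the aim in the Discussion. It works within a group, however, and does not compare YGJ with PWS or with usual care. The optional covariates in section 2.11 could be stretched to cover screening ghrelin, but they are conditional and do not name it.

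What stands is the mismatch between the rule as stated and an outcome with one post-treatment value. That is something the article fixes, not something it leaves out.

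**Conclusion.** The point holds as a minor one. The blanket sentence assigns ghrelin to a model that either reduces to unadjusted change or, read literally on both values, has a group effect aimed at half the week-6 difference. Against a comparison with 80% power under ANCOVA, the first has about 68% to 73% at correlations of 0.5 to 0.7, and the second about 29%, 19% or 14% at 0.5, 0.7 or 0.8. These figures assume equal variances, complete data and correlations that the documents do not give; the 80% is a reference level, not a claim about this trial's power for ghrelin. They do not depend on skewness. The gain from a log scale is a further assumption, about 1 to 5 points at CV up to 0.3 and larger only from about 0.5. Ghrelin is exploratory and secondary, so the primary TDS result and the fixed testing sequence are untouched.

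**What to change.** In section 2.11, exempt serum ghrelin from the rule that secondary outcomes follow the primary method. State that week-6 acyl-, deacyl- and total ghrelin will be compared by ANCOVA with treatment group and the screening value of the same measure as covariate.

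Pre-specify the scale in the same place. For the three concentrations, log both the week-6 and the screening value and report geometric mean ratios with 95% confidence intervals. For the acyl share, analyse log(acyl/deacyl): with share p = acyl/(acyl + deacyl), p/(1 − p) = acyl/deacyl, so this is the logit of the planned ratio.

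The cost is a sentence or two of text, with no new samples, visits or participants. The downside is that results appear as ratios instead of concentration differences.

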#### 2.9.4. Safety Outcomes

The following laboratory parameters will be measured to assess the safety of investigational products at the screening visit and week 6 (Visit 4) in all participants: liver function test (aspartate aminotransferase and alanine aminotransferase), renal function test (blood urea nitrogen and creatinine), complete blood count, and electrolyte content (sodium and potassium). In addition, adverse events will be investigated through participants’ self-reporting and medical examination during the trial period, and the investigator will measure the vital signs (blood pressure, pulse rate, and body temperature) of participants at each visit.

### 2.10. Sample Size Calculation

The primary objective of this study is to compare and evaluate the effectiveness of 6 weeks of administration of YGJ compared to usual care in participants with FD. We will test whether there is a difference in the degree of reduction in TDS scores between the two groups after 6 weeks through a superiority test. Based on the results of a previous study comparing YGJ and a placebo [19], and considering the 15% placebo effect, it is assumed that the difference between the average TDS change between the YGJ and usual care groups after 6 weeks is 2.70, and the standard deviation is 3.65. The significance level is 0.05, and the power is 80%. Taking into account the previous studies [11,19] and ethical issues, the ratio between the YGJ and usual care groups is assigned at 2:1. Therefore, 44 and 22 participants are required for the YGJ and usual care groups, respectively.

Additionally, the second purpose of this study is to evaluate the noninferiority of YGJ compared with that of PWS. For this, the noninferiority margin should be defined based on the results of the effect evaluation between the PWS and usual care groups. However, due to the lack of prior research and related data, we will first test the superiority of PWS compared to usual care after 6 weeks to define the noninferiority margin. Under the assumption that the effect size of the YGJ and PWS is the same, 44 participants are also required in the PWS group. Therefore, considering the 20% dropout rate, a total of 140 participants, including 56, 56, and 28 participants in the YGJ, PWS, and usual care groups, respectively, are required.

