**Hypothesis** **3.**
*[*

$H_{0}\;:\;\mu_{3}-\mu_{1}>M,\;H_{1}\;:\;\mu_{3}-\mu_{1}\;\leq M$

*]*

*-*

$\mu_{1}$

*: Change in TDS score of the YGJ group at week 6*

*-*

$\mu_{3}$

*: Change in TDS score of the PWS group at week 6*

To evaluate the noninferiority of YGJ compared to PWS, Hypothesis 3 will be tested in the same way as Hypothesis 1. However, since the noninferiority test is a single test, the significance level will be set to 2.5%, and the noninferiority margin will be defined as the lower limit of the 95% CI of Hypothesis 2. The multiple test problem will be solved using the fixed sequence method [29]. In other words, if the statistical test result for Hypothesis 1 is significant, the test for Hypothesis 2 will be performed, and if the statistical test result for Hypothesis 1 is not significant, the test for Hypothesis 2 and Hypothesis 3 will not be performed. If the statistical test result for Hypothesis 1 is significant and the test for Hypothesis 2 is performed, and if the statistical test result for Hypothesis 2 is significant, the test for Hypothesis 3 will be performed. If the statistical test result is not significant, the test for Hypothesis 3 will not be performed. If possible, subgroup analysis will be performed by categorizing the participants’ baseline characteristics, including age (65 years old or older/under), Rome IV subtype (EPS, PDS, and overlap), type of FD pattern identification (according to the standard tool for pattern identification of FD [21]: spleen–stomach deficiency and cold, spleen deficiency with qi stagnation, liver–stomach disharmony, cold–heat complex, spleen–stomach dampness and heat, and dietary retention and stagnation), deficiency and excess pattern identification, and the presence or absence of *Helicobacter pylori* infection and spleen qi deficiency syndrome (cut off score: 43.18 points in SQDQ [27]). In addition, we will combine the results of the YGJ and PWS groups corresponding to herbal medicine and compare them with the usual care control group.

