## 3. Discussion

The present study is a protocol for a randomized, assessor-blind, multicenter, controlled clinical trial evaluating the effectiveness and safety of YGJ compared with usual care and PWS in patients with FD, and will be conducted in conjunction with a cost-effectiveness analysis. We aim to test the superiority of YGJ to usual care and noninferiority to PWS for the treatment of FD. In addition, although YGJ is actively used in the Korean medicine clinical field for the treatment of FD, a cost-effectiveness analysis has not yet been conducted for this. We intend to prepare the basic data for health insurance benefit registration of YGJ by confirming the cost-effectiveness of YGJ compared to PWS, the most commonly used health insurance benefiting herbal medicine for the treatment of FD in Korean medicine clinical settings [7]. Based on consultation with Korean medicine gastroenterology experts and prior literature that stated that at least 4–6 weeks of treatment was required to see the significant therapeutic effect of YGJ, we set 6 weeks as the administration period of investigational products [12].

According to the guideline recommendations for outcome measures used in clinical trials for FD [32], the primary efficacy outcome measures to be used in FD clinical trials are diverse and have not yet been standardized. Additionally, in Korea, a patient-reported outcome measure that has been verified as recommended by local or global guidance has not yet been developed. Accordingly, it is recommended to use the total symptom score and OTE as the primary efficacy endpoint for FD clinical trials [32]. Therefore, in our study, the TDS score, which was used frequently as the primary outcome measure in previous studies on FD [11,19,22], was selected as the primary outcome according to the expert consensus, and OTE was set as the secondary outcome. Additionally, based on such previous studies [11,19], a sample size suitable for hypothesis testing was calculated in the present study.

In addition, based on previous studies showing that psychological factors are closely related to the pathogenesis of FD [12,33,34], we will measure HADS as a secondary outcome to determine whether anxiety and depressive symptoms are improved after administration of investigational products and to examine the correlation with other outcomes such as TDS and ghrelin.

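### The 44 PWS participants presented as required under the noninferiority purpose are sized only for PWS versus usual care; under the plan's own rules the noninferiority test has about 23% to 35% power

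*Protocol article*

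**What the plan says.** Section 2.10 sizes the primary comparison, YGJ against usual care, on the week 6 change in TDS. The assumed difference and SD are given as "YGJ and usual care groups after 6 weeks is 2.70, and the standard deviation is 3.65". The error rates follow: "The significance level is 0.05, and the power is 80" per cent. On allocation, "the ratio between the YGJ and usual care groups is assigned at 2:1". The result is that "44 and 22 participants are required for the YGJ and usual care groups, respectively".

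The next paragraph turns to noninferiority of YGJ to PWS. It explains that data for a margin are lacking, so superiority of PWS over usual care will be tested first and used to define the margin. It then states: "Under the assumption that the effect size of the YGJ and PWS is the same, 44 participants are also required in the PWS group". A 20% dropout allowance gives 56, 56 and 28, or 140 in total.

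Section 2.11 sets the tests in a fixed sequence: YGJ versus usual care (Hypothesis 1), PWS versus usual care (Hypothesis 2), then noninferiority of YGJ to PWS (Hypothesis 3). On the gate it says that "if the statistical test result for Hypothesis 1 is not significant, the test for Hypothesis 2 and Hypothesis 3 will not be performed", and Hypothesis 3 also waits on Hypothesis 2. Hypothesis 3 is tested at 2.5%, with the margin equal to the lower 95% confidence limit found for Hypothesis 2.

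The Discussion gives superiority to usual care and noninferiority to PWS as the two aims, and adds: "Additionally, based on such previous studies [11,19], a sample size suitable for hypothesis testing was calculated in the present study".

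**The concern.** A reader of section 2.10 meets the noninferiority purpose, then a number of PWS participants said to be required, and will take that number as adequate for the purpose. It is not a noninferiority size. It is the size that gives 80% power to a single superiority test of PWS against usual care. Hypothesis 3 compares two active arms. It uses a margin cut down by the uncertainty of the Hypothesis 2 estimate, and it is reached only if two earlier tests succeed.

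The Introduction and Discussion tie the PWS comparison to possible insurance listing of YGJ. If the products are in truth equally effective and the test is unlikely to show it, a failed Hypothesis 3 could be taken as YGJ falling short of PWS when it mainly reflects the sample size. Nothing in the article warns of this.

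**Working it through.** **Inputs.** From section 2.10: difference 2.70, SD 3.65, ratio 2:1, evaluable 44/44/22 (YGJ/PWS/usual care), randomised 56/56/28, PWS effect equal to YGJ effect (true YGJ minus PWS difference 0), and change read as reduction in TDS. From section 2.11: two-sided 5% for Hypotheses 1 and 2, 2.5% for Hypothesis 3, the fixed sequence and the margin rule. Assumed here: SD 3.65 holds in every arm and for the model-based week 6 contrast, and the observed margin is used in Hypothesis 3 as if it were a known number.

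**Step 1: the plan's own figure.** Usual care n = (1 + 1/2) × 3.65² × (1.96 + 0.8416)² / 2.70² = 1.5 × 13.3225 × 7.849 / 7.29 = 21.5, so 22, and 44 in YGJ. Power at 44/22 is 80.9% by the normal formula and 79.7% by the noncentral t. Dropout: 22/0.8 = 27.5, so 28; 44/0.8 = 55, raised to 56 to keep 2:1. The total is 56 + 56 + 28 = 140. Everything stated reproduces.

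**Step 2: standard errors at 44/44/22.**
- Either product versus usual care: 3.65 × √(1/44 + 1/22) = 0.953.
- YGJ versus PWS: 3.65 × √(2/44) = 0.778.
- The two comparisons with usual care share that arm, so their correlation is (1/22)/(1/44 + 1/22) = 2/3.

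**Step 3: Hypothesis 3 under the stated rule.** The expected margin is 2.70 − 1.96 × 0.953 = 0.83 points. The 95% half-width for YGJ versus PWS is 1.96 × 0.778 = 1.53 points, nearly twice as large. Write P, Y and U for the observed mean reductions with PWS, YGJ and usual care. Noninferiority requires

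(P − Y) + 1.96 × 0.778 ≤ (P − U) − 1.96 × 0.953.

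P cancels, leaving Y − U ≥ 1.96 × (0.778 + 0.953) = 3.39. The true value is 2.70, so the probability is Φ((2.70 − 3.39)/0.953), about 23%. Adding the requirement that Hypotheses 1 and 2 pass barely changes it (23.0%).

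**Step 4: power through the sequence.** The ranges cover the bivariate normal calculation and t-based simulation (200,000 runs) with pooled and with pairwise SDs.

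| Evaluable | H1 | H1 and H2 | H1, H2 and H3 |
|---|---|---|---|
| 44/44/22 | 80–81% | 70–72% | 22–23% |
| 56/56/28 | 88–89% | 82–83% | 35% |

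At 44/44/22, with equal products, about 29% of trials never reach Hypothesis 3, about 71 − 23 = 48% reach it and fail, and about 23% succeed. Among those that reach it, about 32% succeed.

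**Step 5: size needed.** The margin is an observed confidence limit, so it grows as the trial grows. At 108/108/54 the standard errors are 0.608 and 0.497, the threshold for Y − U is 1.96 × 1.105 = 2.17, and Φ((2.70 − 2.17)/0.608) is about 81%; with the gates it is about 80%. That is 108 + 108 + 54 = 270 evaluable.

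**Step 6: sensitivity to the margin.** With the margin fixed in advance, sequence power at 44/44/22 is about 28% for 1.35, 53% for 2.0 and 67% for 2.70. These margins are illustrations; none is in the article.

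**The case against.** The strongest reply is that nothing has been miscalculated and little has been hidden. The numbers reproduce. The 80% appears once, in the paragraph on the primary objective, and is right there because Hypothesis 1 comes first in the sequence. The sentence before the 44 says that PWS will be tested for superiority over usual care, so the origin of the number is visible. All of this stands. A reader might infer an arithmetic error, or a claim of 80% power for noninferiority; the document supports neither. What remains is that the number is called required within the noninferiority paragraph, and that the Discussion calls the sample suitable for hypothesis testing after naming noninferiority as an aim.

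Second, sizing each superiority comparison on its own and controlling error by a fixed sequence is common practice, and participants lost after week 3 still contribute to a repeated-measures model. This largely answers the Hypothesis 2 shortfall: 71% assumes the full 20% loss leaves no information, and with all 140 evaluable the figure is about 83%. It is a lesser point. The reply does not rescue Hypothesis 3, which stays near 35% with no loss at all. For Hypothesis 3 to reach 80% at 44/44/22, the effective SD would have to fall from 3.65 to about 2.35, and nothing in the article suggests that.

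Third, the Hypothesis 3 result depends heavily on the margin, as step 6 shows. That is correct, so any power quoted must be tied to the margin rule in force. It also rules out a tempting stronger reading, that about 300 per arm are needed. That figure (303) comes from freezing the margin at 0.83, its expected value at 44/22; under the rule in section 2.11 the margin moves with the sample size.

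**Conclusion.** The point holds in a limited form. The 44 in the PWS arm is a stand-alone superiority size for PWS versus usual care, placed under a purpose it does not serve, and no calculation covers Hypothesis 3. Under the article's own assumptions, fixed sequence and margin rule, power to conclude noninferiority is about 23% at the planned evaluable numbers and about 35% with no dropout. Equally effective products would therefore fail to yield the conclusion in roughly two thirds to three quarters of trials. Hypothesis 2 reached through the sequence has about 71% and 83% respectively.

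These figures rest on SD 3.65 in all arms, a true effect of 2.70 for both products, change read as reduction, and the margin rule as written. A different margin rule would change the Hypothesis 3 figure substantially. The primary comparison and its stated power are unaffected. This should be fixed, but it is a matter of stating accurately what the sample can do for a secondary purpose and does not put the design of the primary test in question.

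**What to change.** In section 2.10:

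- State that the 80% power applies to Hypothesis 1.
- State that the PWS arm was sized for Hypothesis 2 taken alone, and that 44 is not a number required for noninferiority.
- Give the power for Hypothesis 3 under the margin rule in force: about 23% at 44/44/22 evaluable and about 35% at 56/56/28 under the present rule. Recompute it if the margin rule changes. The sequence power for Hypothesis 2 (about 71% and 83%) can be given alongside.

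In section 2.11, state that the YGJ minus PWS difference will be reported with its 95% CI whatever the outcome of the sequence, and that failure of Hypothesis 3 will be read as inconclusive, not as evidence of inferiority. Bring the Discussion sentence on the suitability of the sample size into line, limiting it to the comparisons with usual care.

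The cost is wording in the protocol and, where one exists, the analysis plan. Enrolment, allocation and the primary analysis do not change. The downside is that the stated power for the second purpose becomes less favourable.
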